Primary outcome(s)	1. Effectiveness: Depression severity (mean change) measured using Patient Health Questionnaire-9 (PHQ-9) at the 6-month timepoint 2. Implementation: Reach of depression treatment (RT) using RT = st/ne, where ‘st’ represents the number of individuals who participated in the treatment for depression and ‘ne’ represents the number of people eligible for such treatment at 6 months

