Key secondary outcome(s)	The following secondary outcomes related to clinical effectiveness will be measured at the participant level during follow-ups at 3, 6, and 12 months, unless otherwise specified below: 1. Body mass index (BMI) calculated using the formula: BMI = weight (kg)/height (m^2^), where height is measured in metres and weight is measured in kilograms 2. Blood pressure measured using an automated blood pressure instrument 3. Waist circumference measured in centimetres 4. Depression severity measured using PHQ-9 at 3 and 12 months 5. Depression caseness measured using PHQ-9 6. Anxiety caseness and severity measured using Generalised Anxiety Disorder Questionnaire (GAD-7) 7. Quality of life measured using Euroqol’s instrument EQ-5D-5L 8. Functional impairment measured using the WHO Disability Assessment Schedule (WHODAS 2.0) at 6 and 12 months 9. Healthcare resource measured using modified Client Service Receipt Inventory (CSRI) at 6 and 12 months 10. Adverse events measured using a modified adverse event The following clinic-level aggregated secondary outcomes related to implementation effectiveness will be calculated at 3, 6, and 12 months follow-up timepoints, unless otherwise specified below: 11. Reach of screening (RS) calculated using the formula RS = sd/nc, where ‘sd’ represents the number of individuals screened for depression and ‘nc’ denotes the total number of individuals attending the clinics 12. Reach of depression treatment (RT) calculated using RT = st/ne, where ‘st’ represents the number of individuals who participated in the treatment for depression and ‘ne’ represents the number of people eligible for such treatment at 3 and 12 months 13. Adoption (AD) calculated using AD = r/nr, where ‘r’ denotes the number of people referred for the treatment of depression and ‘nr’ denotes the number of people eligible for referrals at 3, and 6 months 14. Treatment enrolment (TE) calculated using TE = te/ne, where ‘te’ represents the number of people enrolled in the treatment of depression and ‘ne’ represents the number of people eligible for such treatment 15. Treatment completion (TC) calculated using TC = tc/te, where ‘tc’ represents the number of people completed the depression treatment and ‘te’ the number of people enrolled in such treatment 16. Treatment drop (TD) calculated using TD = td/te, where ‘td’ represents the number of people dropped out of the depression treatment and ‘te’ the number of people enrolled in such treatment 17. Sustainability calculated using change in percentage from baseline to follow-up time-points in reach, adoption, treatment enrolment, completion, and dropout 18. Equity by comparing reach, adoption, treatment enrolment, completion, and dropout across different levels of socioeconomic status, gender, and ethnicity

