#### Primary outcome—implementation

Our primary outcome is the reach of depression treatment, measured by calculating the proportion of eligible individuals (score on PHQ-9 ≥ 10) who participate in treatment for depression (having ≥ two contacts with healthcare staff) 6 months after the CC rollout in the clinics, i.e. when clinic staff start practising CC in their clinics, referred to as the ‘start date’.

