#### Secondary outcomes—implementation

Secondary implementation outcomes include:The reach of screening as the percentage of people attending clinics who participated in screening for depression (PHQ-2 and PHQ-9) at least once.Adoption of the intervention will be determined at 3 and 6 months through referral rates (number of patients referred for treatment divided by number of eligible patients). We will consider referrals, including within primary care settings and to specialised facilities if required. We will track the number of healthcare staff invited to training, those who attend, and the average number of supervision or case review meetings attended by staff each month. These metrics will be assessed in the 3rd and 6th month follow-up after the start date.The implementation of the CC components will be assessed using treatment engagement and dropout rates. We will determine the enrollment, completion, and dropout rates for psychotherapy (BA therapy in intervention clinics and any psychotherapy delivered in control clinics). Individuals who attend ≥ 2 sessions will be categorised as ‘engaged with BA/any psychotherapy’, whereas those attending < 2 sessions will be considered dropouts. We will also evaluate the prescription and adherence rates of antidepressants using the total number of antidepressants prescribed and the participants who complete their prescribed course of antidepressant medication captured through patient self-reporting.Sustainability will be assessed by comparing reach, BA completion and dropout, antidepressant prescription, and compliance rate over time.Equity in the treatment is the just distribution of treatment services, ensuring the participation of all individuals regardless of their socioeconomic status (SES) and demographic backgrounds. To ascertain equity, we will compare implementation outcomes mentioned above by SES and demographics (age, sex, ethnicity, education level).

Unless otherwise stated above, all outcomes will be recorded and compared across allocation groups, where feasible at all time points (3, 6, and 12 months after the start date).

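### Completion, dropout and (where contacts follow eligibility) reach are counted at clinic-clock cuts with no per-person window, so sustainability can appear to rise while performance is constant

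*Protocol article*

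**What the plan says.** The Protocol article runs two clocks. Under Outcomes, individual-level follow-up starts at each participant's recruitment. Table 3 starts clinic-level data once collaborative care (CC) has been set up.

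- **Reach (primary implementation outcome).** The proportion of people with PHQ-9 of 10 or more who have at least two contacts with healthcare staff, taken "6 months after the CC rollout in the clinics, i.e. when clinic staff start practising CC in their clinics". In Table 1 the denominator "represents the number of people eligible for such treatment at 6 months". Table 1 also lists reach at 3 and 12 months as a secondary outcome.
- **Completion.** Table 1, item 15: "Treatment completion (TC) calculated using TC = tc/te", where the numerator is those who completed and the denominator is all enrolled.
- **Dropout.** Under Secondary outcomes—implementation, those attending fewer than "2 sessions will be considered dropouts".
- **Timing.** In the same section, unless otherwise stated, "all outcomes will be recorded and compared across allocation groups, where feasible at all time points (3, 6, and 12 months after the start date").
- **Sustainability.** Table 1, item 17: "Sustainability calculated using change in percentage from baseline to follow-up time-points in reach, adoption, treatment enrolment, completion, and dropout". The outcomes text likewise compares reach, completion and dropout over time.

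Entry is continuous: Recruitment and Optimised usual care have all adult attenders screened as routine practice in both arms. The article gives no entry cut-off, no minimum time since eligibility or enrolment, and no category for people still in treatment.

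**The concern.** Someone enrolled a week before a cut is in the denominator of completion but cannot yet have finished a course. If they have had one session, the dropout rule classes them as a dropout. Someone found eligible that week is in the denominator of reach, perhaps before a second contact could be arranged. These recent entrants are a large share of everyone seen by 3 months and a small share by 12 months. The percentages therefore drift in the favourable direction without any change in care.

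Sustainability is read from that drift. A measure meant to detect fading performance could show improvement while performance is flat or falling. The primary reach comparison is also exposed if one arm makes its second contact faster than the other. Reach additionally feeds the implementation cost-effectiveness analysis.

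**Working it through.** **Inputs.** From the Protocol article: the ratios, the cuts at 3, 6 and 12 months (13, 26 and 52 weeks), the two-contact and two-session thresholds, and continuous entry. The article gives no expected reach or completion, course length or time to second contact, so there is no stated figure to reproduce. Assumed: steady entry, cumulative counting, a true eventual proportion p = 60%, and a lag of L weeks from entry to the qualifying event.

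**Formula.** With steady entry over T weeks and a fixed lag, only those who entered before T − L can have had the event, so the observed proportion is p × (1 − L/T).

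**Constant true 60%:**

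| Lag | 3 months | 6 months | 12 months |
|---|---|---|---|
| 2 weeks | 50.8% | 55.4% | 57.7% |
| 4 weeks | 41.5% | 50.8% | 55.4% |
| 6 weeks | 32.3% | 46.2% | 53.1% |
| 8 weeks | 23.1% | 41.5% | 50.8% |
| 12 weeks | 4.6% | 32.3% | 46.2% |

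For example, 8 weeks at 3 months: 0.60 × (1 − 8/13) = 0.231. For courses of 6, 8 and 12 weeks, the false rise in completion from 3 to 12 months is about 21, 28 and 42 points.

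**Sensitivity to lag shape.** With an exponential lag of mean L, the observed proportion is p × [1 − (L/T)(1 − exp(−T/L))]. Means of 6, 8 and 12 weeks give 35.5, 30.3 and 23.4% at 3 months and 53.1, 50.8 and 46.3% at 12 months, a rise of about 18 to 23 points.

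**A hidden decline.** Let true completion be 70% for entrants in weeks 0-13, 65% in weeks 13-26 and 60% after that, with an 8-week lag:
- 3 months: 0.70 × 5/13 = 26.9%
- 6 months: (0.70 × 13 + 0.65 × 5)/26 = 47.5%
- 12 months: (0.70 × 13 + 0.65 × 13 + 0.60 × 18)/52 = 54.5%

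The true cumulative values fall: 70.0, 67.5 and 63.8%.

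**Dropout.** If 60% eventually attend two sessions and the second comes 2 weeks after enrolment, dropout reads 100 − 50.8 = 49.2%, then 44.6%, then 42.3%, against a true 40% throughout.

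**Arm comparison of reach at 6 months.** With equal true reach and lags a and b, the ratio is (26 − a)/(26 − b):
- equal lags: 1.00
- 1 v 2 weeks: 25/24 = 1.04
- 2 v 4 weeks: 24/22 = 1.09
- 2 v 6 weeks: 24/20 = 1.20

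Equal lags with different entry timing also matter. If entry is steady in one arm and rises linearly from zero in the other, the ratio is 1/(1 − L/26), which is 1.08 for a 2-week lag and 1.18 for 4 weeks.

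**Other counting rules, 4-week lag, true 60%.** Following entrants only within their own period (0-3, 3-6, 6-12 months) gives 41.5, 41.5 and 50.8%. Dividing events in a period by entrants in that period gives 41.5% in the first period and 60% afterwards.

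**Effect of the fix.** With a per-person window at least as long as the longer lag, constant 60% reads 60% at every cut and the arm ratio is 1.00. If late entrants are excluded instead of followed, a 4-week window keeps 69, 85 and 92% of entrants at 3, 6 and 12 months, and an 8-week window keeps 38, 69 and 85%.

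**The case against.** The article condenses a fuller protocol, never says that counts are cumulative, and may leave data-cut rules to the statistical analysis plan. That is fair as far as an explicit accumulation rule goes. But the article does fix the ratios, the cuts, the dropout threshold and the sustainability measure, and applied as written these produce the drift. This is more than missing detail.

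Three stronger readings are tempting, and the documents do not support them.

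- **That the primary arm comparison is biased.** No passage shows that time to second contact or entry timing differs between arms. Both use the same PHQ-2 then PHQ-9 pathway, with counsellors hired where absent. With equal pace and entry, dilution cancels in the log-link risk ratio. A difference is possible, because the arms deliver different treatments and CC adds contact tracking and weekly case review, but its size and direction are unknown.
- **That reach is affected however contacts are defined.** If the physician's screening and the counsellor's PHQ-9 count as the two contacts, the lag is close to zero and the reach artefact nearly disappears.
- **That every counting rule gives the same trend.** With period events over period entrants, only the first period is short.

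Two further points stand. Reach achieved by 6 months after rollout is a legitimate service-level quantity, and its dilution is modest: 2/26 = 8% to 4/26 = 15% in relative terms for lags of 2 to 4 weeks. The large figures concern completion, a secondary outcome whose course length is not stated. If completion meant only two sessions with a 2-week lag, the false rise would be about 7 points (50.8 to 57.7%).

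**Conclusion.** The point holds for completion, dropout and the sustainability measure built on them. It holds for reach where the qualifying contacts come after the eligibility PHQ-9. On the plain reading, completion at a constant 60% would read 5-32% at 3 months and 46-53% at 12 months for 6-12 week courses, and a real decline can appear as a rise. This needs no difference between arms. Table 3 also places BA completion and dropout in the baseline column, just after CC set-up, when newly started BA cannot yet be complete; that would steepen the trend.

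A false arm difference in primary reach is conditional: 1.00 with equal pace and entry, about 1.04 to 1.20 under the unequal delays shown. It should be reported as a risk that the definition leaves open, not as a demonstrated bias.

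All sizes rest on assumed lags, steady entry, cumulative counting and the 60% level.

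**What to change.** Define reach, completion and dropout on entry cohorts, with the same fixed window for every person and both arms. The window runs from the qualifying PHQ-9 for reach and from enrolment for completion and dropout. For completion it should cover at least one full course.

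Keep the cuts, but extract the data one window after each cut so that every entrant is followed for the full window. If that is not possible, leave out people who entered within one window of the cut.

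Assess sustainability by comparing successive non-overlapping entry cohorts (for example months 0-3, 4-6 and 7-12) with that same window. State which contacts count towards reach. State also what serves as the start date in control clinics, since it is defined by staff practising CC. Settle these definitions before reach is analysed.

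The cost is a change of definition, plus dated entries for eligibility, contacts and completion in both arms. A screening register and counsellor tracking are planned as part of the CC implementation, but equivalent dated records in control clinics need confirming, and the plan otherwise relies on aggregated data. Extraction moves a few weeks later. The exclusion route costs most at 3 months, where an 8-week window would keep only about 38% of entrants, so later extraction is preferable. No additional patient contact is needed.

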### Sample size

We calculated our sample size based on a recent meta-analysis of CC [13] with a pooled standardised effect size of − 0.51 (95% confidence interval (CI) − 0.80 to − 0.23) for depression outcomes measured up to 6 months. Using an estimate closer to the lower bound, i.e. − 0.35, which is approximately equivalent to 1.4 points on PHQ-9 (assuming SD = 4), we will require 720 participants from 24 clinics (~ 30 participants per clinic) and need to screen approximately 12,000 (assuming 10% depression prevalence, 60% consent rate, 20% attrition, − 0.35 standardised effect, 90% power, 5% alpha, 0.03 intraclass correlation coefficient and design effect of 1.69) to evaluate the clinical effectiveness of CC for depression.

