## Methods

### Study design

The study design is an effectiveness-implementation hybrid type-II trial with cluster randomisation to evaluate CC in primary care clinics in Karachi, Pakistan. A mix of qualitative and quantitative methods will be used to collect data on clinical effectiveness, and implementation outcomes. An embedded process evaluation will help to understand implementation processes, and an economic evaluation will assess cost-effectiveness. Trial registration data is presented in Table 1. The SPIRIT reporting checklist is included as additional information [34].

**Table 1 Tab1:** Trial registration data

Data category	Information
Primary registry and trial identifying number	ISRCTN ISRCTN13462277
Date of registration in primary registry	October 07, 2024
Source(s) of monetary or material support	NIHR under Global Health Research Centre programme (NIHR203248)
Primary sponsor	The University of York, UK
Contact for public inquiries	[name]
Contact for scientific queries	[name]
Public title	Improving services for identifying and treating depression in primary healthcare clinics
Scientific title	Strengthening Primary care for Recognising and Treating Depression (SPiRiT-D)
Countries of recruitment	Pakistan
Health condition(s) or problem(s) studied	Depression
Intervention(s)	The intervention involves implementing a collaborative care model for depression in primary healthcare units. This model includes five key components: systematic identification of depression, provision and adjustment of evidence-based care (both antidepressants and brief behavioural treatment), tracking treatment outcomes, and weekly case review and supervision meetings. A collaborative care model for identifying and managing depression will be introduced in all intervention clinics using various implementation strategies
Key inclusion and exclusion criteria	Inclusion criteria: 1. Attending primary care clinics, 2. Aged 18 years or above, 3. Score on PHQ-9 ≥ 10 Exclusion criteria: 1. Participants already receiving any kind of treatment for depression, 2. Participants lacking the capacity to provide informed consent, or not willing to consent
Study type	Effectiveness-implementation hybrid type II cluster randomised controlled trial with an embedded economic and a mixed-methods process evaluation
Date of first enrolment	June 02, 2025
Target sample size	750
Recruitment status	Recruiting

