### Statistical methods

Statistical analysis will be conducted using STATA version 18 (StataCorp, College Station, TX). All statistical tests will use 5% significance levels and 95% confidence intervals. Descriptive statistics (mean, standard deviation, counts, and percentage) shall be used to summarise both effectiveness and implementation outcomes at baseline and 3-, 6-, and 12-month follow-up time points by allocation groups. Assumptions of all parametric tests (such as normal distribution) where applicable and the presence of missing data at random will be evaluated; if not met, appropriate transformation or multiple imputation methods will be considered.

A mixed effects linear regression model will be used with a PHQ-9 score at 6 months as the outcome for the primary effectiveness endpoint. We will use the PHQ-9 baseline score and other important baseline variables as fixed effects and clinics as random effects to account for the clustered nature of the data. The same models (or logistic mixed effects model in case of binary outcome) will be used for other individual-level secondary variables, where applicable. All the analyses will be based on the intention-to-treat principle.

On the other hand, generalised linear model with a log link function and binomial distribution will be used for ‘reach’ (participants who received treatment divided by those eligible for treatment) as an aggregated implementation outcome to compare allocation groups while using some important clinic-level factors as covariates such as availability of EMR (present vs absent) and average attendance per month (small < 1000, medium 1001–3000, large > 3000). All other clinic-level data will be analysed using the same model, where comparisons across groups are applicable. Some clinic-level data captured only in the intervention group, such as adoption, will be summarised using descriptive statistics.

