### Trial status

This is the current approved protocol version (V0.7), dated September 05, 2024. Recruitment began in May 2025 and is ongoing, expected to complete by March 31, 2026. Until 15th January 2026, 83% of the target recruitment has been achieved, which is 598/720 trial participants recruited.

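### Table 1 gives a target of 750 where the calculation and trial status use 720, and the stated 90% power is a normal-approximation figure (about 87% on 22 df before baseline adjustment)

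*Protocol article*

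**What the plan says.** The sample size section of the protocol article requires 720 participants from 24 clinics, about 30 each. It takes a standardised effect of 0.35 in absolute value, "which is approximately equivalent to 1.4 points on PHQ-9 (assuming SD = 4"), with 20% attrition and "90% power, 5% alpha, 0.03 intraclass correlation coefficient and design effect of 1.69". It expects to screen about 12,000 people, assuming 10% prevalence and 60% consent.

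The trial status section uses the same denominator: "598/720 trial participants recruited", reported as 83% of target. Table 1 under Study design, which holds the registration data, instead reads "Target sample size 750". No explanation of the additional 30 is given.

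Under Statistical methods, the primary effectiveness analysis is a mixed linear model for 6-month PHQ-9 with clinic as a random effect and baseline PHQ-9 among the fixed effects. The same section says "All statistical tests will use 5% significance levels and 95% confidence intervals". The article names no sample size formula, no degrees-of-freedom method and no baseline-outcome correlation.

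**The concern.** There are two separate matters.

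First, the article prints two recruitment targets as current text. A sample size is a figure against which a trial is later judged. If 750 stays in the registration table and the trial closes at 720, a reader will see an unexplained shortfall. Recruitment was still open at the date of the status report, so this can be settled before it closes.

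Second, treatment is allocated to 24 clinics, so the treatment contrast is estimated between clinics. With 12 per arm, an unadjusted comparison has at most 22 degrees of freedom. A normal-approximation formula with a design effect corrects the variance for clustering but still uses a normal critical value. If the stated 90% was obtained that way, it is a little higher than the listed inputs support under a t reference.

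**Working it through.** **Inputs (sample size section unless noted).** Effect 0.35 SD (1.4/4); alpha 0.05, taken as two-sided because Statistical methods pairs the 5% level with 95% intervals; power 90%; ICC 0.03; design effect 1.69; attrition 20%; 24 clinics of about 30. Allocation is 1:1 (Abstract, Methods), so 12 clinics per arm.

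**Step 1: reproduce the plan's figure.**
- Analysed per clinic: 30 × 0.8 = 24. Design effect: 1 + (24 − 1) × 0.03 = 1.69, as stated.
- Per arm without clustering: 2 × (1.96 + 1.2816)² / 0.35² = 171.5, so 343.1 in total.
- With clustering: 343.1 × 1.69 = 579.8 analysed; 579.8 / 0.8 = 725 recruited. Rounding up to 172 per arm first gives 727. Either is close to 24 × 30 = 720.
- In reverse, 720 × 0.8 = 576 analysed, 288 per arm. SE = √(2 × 1.69 / 288) = 0.1083 SD. Noncentrality = 0.35 / 0.1083 = 3.231. Normal power = Φ(3.231 − 1.96) = 89.8%.

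The stated 90% is therefore the normal-approximation result.

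**Step 2: which target do the other figures fit?**

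| Figure in the article | With 720 | With 750 |
|---|---|---|
| About 30 per clinic | 720/24 = 30 | 750/24 = 31.25 |
| Design effect 1.69 | 1 + 23 × 0.03 = 1.69 | 25 analysed per clinic: 1 + 24 × 0.03 = 1.72 |
| Screen about 12,000 | 720/(0.10 × 0.60) = 12,000 | 12,500 |
| 598 recruited is 83% | 598/720 = 83% | 598/750 = 80% |

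All four fit 720.

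**Step 3: same inputs, t reference.** The degrees of freedom are 24 − 2 = 22, and the two-sided 5% critical value is 2.074 instead of 1.96.
- 720 recruited: noncentral t with noncentrality 3.231 gives **87.0%**.
- 750 recruited: SE = √(2 × 1.72 / 300) = 0.1071, noncentrality 3.269; normal 90.5%, noncentral t **87.8%**.
- Effect detectable with 90% power at 720: the noncentrality needed on 22 df is 3.393, and 3.393 × 0.1083 = 0.37 SD (0.3676), or 1.47 points at SD 4.

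**Step 4: what the calculation leaves out (assumed ranges).**
- Baseline adjustment, if SD 4 is the unadjusted SD and the variance falls by 1 − r², on 21 df: r = 0.3 gives 89.8%, r = 0.4 gives 91.9%, r = 0.5 gives 94.5%.
- Unequal clinic sizes, with design effect 1 + [(1 + CV²) × 24 − 1] × 0.03, on 22 df and unadjusted: CV 0.2 gives 86.5%, CV 0.3 gives 85.8%, CV 0.4 gives 84.8%.

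The article gives neither r nor CV.

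**The case against.** **On the target.** The trial visibly counts towards 720 and the figure 750 occurs once, so this is an editorial slip. That largely stands. A reader might infer that the stopping number is truly ambiguous. The documents do not support that, because the status report measures progress against 720. The conflict still has to be corrected, since both numbers are current text and one of them is labelled as the target.

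**On power.** The stated inputs agree with one another and the arithmetic is not wrong; the design-effect formula is standard, and a t reference is a refinement. The 22 degrees of freedom are inferred from the clinic count, and an article may leave the degrees-of-freedom method to the analysis plan. Most of this stands. What remains is narrower: the article itself prints a power figure with its list of assumptions, and on that list 90% is reached only by treating 24 clinics as if they carried unlimited degrees of freedom.

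**The stronger reading.** A reader might infer that the design fails to deliver 90% power. The documents do not support this. The 87% is for an unadjusted comparison with equal clinic sizes, which is not the planned analysis. The planned model includes baseline PHQ-9, and a modest correlation would recover the difference. Nor can unequal recruitment be read off the clinic-size categories: those describe monthly attendance and serve the minimisation, while the plan is about 30 participants in every clinic. The CV values above are assumptions only.

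**Conclusion.** The target conflict is firm and rests on the text alone: 750 in Table 1 against 720 in the sample size and trial status sections, with every derived figure fitting 720.

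The power point is smaller and conditional. On the listed inputs, 90% is the normal-approximation value (89.8%). An unadjusted comparison of 12 against 12 equal-sized clinics on 22 df gives about 87%, a difference of roughly 3 percentage points, or 0.37 SD in place of 0.35 SD for 90% power. Three things are inferred: the two-sided test, the normal method (from the match in step 1) and the 22 df. Choosing 750 would not remove the gap (87.8%). An assumed baseline-outcome correlation of about 0.3 or more would. Nothing here shows that the adjusted primary analysis is underpowered, and the validity of the trial is not in question.

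**What to change.** - **Target.** Give one number in Table 1, the sample size section and trial status. The calculation supports 720. If 750 is intended, say where it comes from and bring the design effect, the screening number and the progress percentage into line with it.
- **Power.** Either restate it as about 87% for 0.35 SD (equivalently 90% for about 0.37 SD, 1.47 points at SD 4) on 22 df before baseline adjustment, or keep 90% and state the baseline-outcome correlation it relies on, with its source.

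The cost is a correction to the wording of the protocol and, if the registry carries 750, to the registry entry, plus a slightly less favourable power figure if the first option is taken. Recruitment, conduct and the primary analysis do not change.
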